### Study design

2.2

We will conduct a two-arm RCT with repeated measures to evaluate the effects of Powerly compared to a control group receiving CAU. Assessments will occur at baseline, after four weeks of app use, and six weeks postpartum (Heller et al., 2020), see Fig. 2. The trial has been approved by the local ethics committee at the University of Zurich (approval #24.08.23) and has been registered with ClinicalTrials.gov (NCT06610552). The data collection will start in November 2024 until the desired sample size is reached. All procedures will be performed in accordance with the Declaration of Helsinki and its subsequent amendments. All participants will be asked to provide informed consent.

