### Participants

2.3

We will recruit participants mainly in Switzerland, Germany and Austria. Volunteers between 24 and 32 weeks pregnant will be included in the trial. Previous similar studies often included women in this range (Guo et al., 2020; Müller et al., 2020; Yang et al., 2019). Other inclusion criteria are being over the age of 18, owning an iPhone (due to technical limitations), and having sufficient fluency in German language. The exclusion criteria include high-risk pregnancies as self-reported, current substance abuse and history of psychiatric disorders such as bipolar disorder, schizophrenia, or other psychotic disorders, current use of professional face-to-face psychotherapeutic support, participation in other clinical trials or interventions at the same time.

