### Procedure

2.5

Participants will be recruited through multiple channels, primarily via gynecology wards in hospitals, gynecology and midwifery practices, and other pregnancy-related services such as birthing classes, prenatal yoga, and parenting workshops. To ensure a diverse sample with various backgrounds, we will also promote the study online through social media platforms targeting pregnant women. Volunteers interested in participating in the study will complete a brief online form providing basic demographic information (age, gender, education) and respond to questions regarding exclusion criteria. Those who meet the inclusion criteria will be contacted by a researcher and assigned a personal code for use throughout the study. The baseline assessment will be conducted online to accommodate participants who may have difficulties traveling while pregnant. Group allocation will be determined using a randomization algorithm generated by a National Institutes of Health clinical trial randomization tool, and the study personnel will be blinded to the group allocation. Participants in the intervention group after completing the baseline questionnaires, will receive instructions on how to download Powerly. They will be encouraged to use the app daily for 28 days, at least once per day, and will be invited to complete the questionnaires again. The duration and frequency of the intervention are based on previous research on CBT-based apps, which found that a four-week period with at least one interaction per day is both common and sufficient to achieve significant improvements in mental health outcomes while ensuring high adherence to the intervention and low drop-out rates (Birney et al., 2016; Marciniak et al., 2020). Participants in the CAU group will complete baseline questionnaires and be informed that they will receive access to Powerly six weeks postpartum. After 28 days, they will be invited to complete the questionnaires again, in a similar manner to Powerly group. Both groups will be contacted around their expected delivery date to confirm the birth date, and again six weeks postpartum for a final follow-up. After this, the CAU group will receive access to Powerly.

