#### Sample size calculation

2.6.1

The sample size calculation for linear mixed models was determined using Cohen's d = 0.5, a mean effect size observed in prior studies investigating digital interventions in pregnant women, where the estimates have ranged from d = 0.4 to d = 0.65 (Heller et al., 2020; Jiao et al., 2019; Qin et al., 2022; Sawyer et al., 2019; Shorey et al., 2019). With a power of 80 % and a significance level of 0.05, the anticipated sample size was 67 participants per group. To account for dropouts, based on our previous studies with similar mobile apps (Marciniak et al., 2024b; Marciniak et al., 2024c), we will aim to include 70 participants per group.

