#### Primary and secondary outcomes

2.6.2

The adherence will be determined as the sum of all interactions with the app by each study participant, specifically: the number of completed entries, and the total time spent on engagements with Powerly.

The questionnaire scores will be calculated according to the manuals, including the relevant subscales. The primary statistical method for other primary and secondary outcomes will be linear mixed models, with time points (baseline versus follow-up I versus follow-up II) and group (Powerly versus CAU) as fixed effects, and participants as random effects. We will employ intention-to-treat analyses, in which we will include all randomized participants, regardless of their app use, complemented by as-treated analyses, including participants who will complete at least one module per day. If necessary, data transformation of dependent variables will be performed based on visual inspection of the data to ensure that the model assumptions are met. Secondary outcome measures will be utilized both as independent variables to assess the effectiveness of Powerly on these outcomes, and as moderators to further explore the Powerly's effect on primary outcome measures. Other covariates which may be used in the analysis include age, number of children, financial situation and stressors encountered by the participants.

The analyses will be conducted using R in R Studio.

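### A participant random intercept assumes equal correlation across unequally spaced visits; if correlation declines with time, change-from-baseline standard errors are too small postpartum and too large at four weeks

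*Protocol article*

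**What the plan says.** Section 2.6.2 (Primary and secondary outcomes) of the protocol article names linear mixed models as the primary method, "with time points (baseline versus follow-up I versus follow-up II) and group (Powerly versus CAU) as fixed effects" "and participants as random effects". It names no random slope, visit-specific variance, residual correlation structure or robust standard error. The only stated response to doubtful model assumptions is to transform the outcome after looking at the data. No group-by-time interaction is written out.

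On timing, section 2.2 (Study design) says: "Assessments will occur at baseline, after four weeks of app use, and six weeks postpartum". Section 2.3 (Participants) says: "Volunteers between 24 and 32 weeks pregnant will be included in the trial". Section 2.5 (Procedure) ties the last visit to the actual birth: "Both groups will be contacted around their expected delivery date to confirm the birth date, and again six weeks postpartum for a final follow-up".

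**The concern.** A random intercept with independent residuals implies compound symmetry: the same variance at each visit and the same correlation between any two visits. The first two visits are four weeks apart and normally both fall in pregnancy. The third comes months later, on the other side of delivery. Two pregnancy scores four weeks apart may well agree more closely than a pregnancy score and a postpartum score.

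The model estimates a single within-person variance and uses it for both changes from baseline. If the true variances of those changes differ, the pooled value is too small for one and too large for the other. With declining correlation, the optimistic error falls on the postpartum change, and the app's stated purpose is to prevent postpartum depression and anxiety. Transforming the outcome does not make the correlations equal.

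**Working it through.** **The plan's own figure.** Section 2.6.1 says the sample size "was determined using Cohen's d = 0.5", with 80% power and "a significance level of 0.05", and arrives at 67 per group. Two-sided, the normal formula 2 x (1.96 + 0.842)^2 / 0.5^2 = 62.8 gives 63, and the two-sample t-test gives 64. A t-test size adjusted for rank-test efficiency (3/pi) gives exactly 67. Power at 67 per group by t-test is 81.9%. The figure is reasonable, uses no within-person correlation, and is not affected by this point.

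**Visit spacing.** Entry is at 24 to 32 weeks, so follow-up I is at 28 to 36 weeks. Birth at 40 weeks is an assumption. Follow-up II is then at 46 weeks on the same scale. The gap from follow-up I is 46 - 36 = 10 to 46 - 28 = 18 weeks, and the gap from baseline is 46 - 32 = 14 to 46 - 24 = 22 weeks. For births at 37 to 42 weeks, the gap from follow-up I runs from 7 to 20 weeks.

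**Formula.** Take complete data, equal arms, a group-by-time interaction and a random intercept.

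- Variance of a change that the model uses: 2 x (mean variance - mean covariance).
- True variance of the change to visit j: Var(Yj) + Var(Y0) - 2 Cov(Y0, Yj).
- Ratio k of model to true standard error: the square root of the first divided by the second.
- Actual two-sided type I error at nominal 5%: 2 x (1 - Phi(1.96 k)).

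The arm size cancels out of k.

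**Worked case.** Correlations are listed as baseline-FU I / baseline-FU II / FU I-FU II. All are assumptions. With 0.7/0.5/0.5 and unit variances, the mean correlation is 1.7/3 = 0.567, so the model uses 2 x 0.433 = 0.867 for both changes. The true values are 2 x 0.3 = 0.6 at FU I and 2 x 0.5 = 1.0 at FU II. So k is sqrt(0.867/0.6) = 1.20 at FU I and sqrt(0.867/1.0) = 0.931 at FU II.

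**Declining correlation, equal variances:**

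| Correlations | FU I: k, type I error | FU II: k, type I error |
|---|---|---|
| 0.6/0.5/0.5 | 1.08, 3.4% | 0.97, 5.8% |
| 0.65/0.5/0.5 | 1.13, 2.6% | 0.95, 6.3% |
| 0.7/0.5/0.5 | 1.20, 1.9% | 0.93, 6.8% |
| 0.8/0.4/0.4 | 1.53, 0.3% | 0.88, 8.4% |

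A simulation of 0.7/0.5/0.5 with 70 per arm (40,000 runs) gave 7.1% at FU II and 1.9% at FU I, in line with the formula.

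**Power at four weeks.** With 0.7/0.5/0.5, 67 per arm and a difference of 0.5 SD, the true standard error is sqrt(2 x 0.6/67) = 0.134 and 0.5/0.134 = 3.74. Power is Phi(3.74 - 1.96) = 96% with the correct standard error and Phi(3.74 - 1.96 x 1.20) = 92% with the pooled one.

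**Patterns that behave differently:**

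| Assumed pattern | k at FU I | k at FU II |
|---|---|---|
| All correlations 0.6, equal SDs | 1.00 | 1.00 |
| 0.6/0.5/0.75, equal SDs | 0.98 | 0.88 |
| 0.5/0.55/0.5, equal SDs | 0.98 | 1.04 |
| 0.7/0.5/0.55, SDs 1, 1.2, 0.8 | 1.07 | 1.02 |

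**Other tests from the same model:**

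- Group difference at a single visit, equal variances: k is 1.00 at both visits.
- The same difference with SDs 1, 1, 1.2: the pooled SD is sqrt(3.44/3) = 1.071, so k at FU II is 1.071/1.2 = 0.89 and the type I error about 8.0%.
- Joint two-degree-of-freedom group-by-time test, equal variances: simulated type I error was 5.0 to 5.3% for the first three patterns in the upper table, and 6.2% at 0.8/0.4/0.4.

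**The case against.** The strongest reply is that the article never says intercept only. Naming participants as the random effect identifies the grouping factor, and the covariance structure may be settled in a full analysis plan that is not shown. That limits the force of the point but does not remove it. A random intercept is the ordinary reading of the sentence, and if a fuller plan says otherwise, the sentence should be brought into line with it.

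The second reply is that the error depends on unknown quantities and on the test chosen. This stands. A reader might infer that the planned standard errors are wrong as a matter of fact, with an inflated error rate for the main postpartum claim. The documents do not support that. They give no correlations or standard deviations, equal values would give no error, and other patterns move the errors elsewhere. They also do not name the change-from-baseline contrast on which the calculation rests. A joint interaction test is barely affected in the moderate cases.

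The third reply concerns scope, and it also stands. The maternal-fetal attachment scale is given at two visits and the postpartum bonding questionnaire at one (section 2.4.2.2), so neither is a three-visit outcome. The schedule of the postpartum depression scale is in Fig. 2, which is not shown, so it cannot be assumed that this primary measure has a baseline value.

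**Conclusion.** The point holds conditionally. The stated model, on its natural reading, makes an assumption that the visit schedule renders doubtful, and the article offers no remedy that would address it. Under declining correlation with equal variances, the standard error of the postpartum change contrast is about 3 to 12% too small, and that of the four-week contrast about 8 to 53% too large. The upper end needs a fall in correlation from 0.8 to 0.4. In the moderate cases the postpartum type I error is 5.8 to 6.8%, and four-week power in the worked case stays well above the planned 80%.

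These figures rest on assumed correlations, complete data, a two-sided test, birth at 40 weeks for the spacing, and an interaction term that the article does not write out. They concern only outcomes measured at all three visits. The point justifies a cheap improvement to the model sentence, not a statement that the analysis is invalid.

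**What to change.** For outcomes measured at all three visits, replace the random intercept with categorical visit, group, the group-by-visit interaction and an unstructured 3x3 residual covariance. Fit by REML with Kenward-Roger or Satterthwaite degrees of freedom. Keep the random-intercept model as the named fallback if the fit does not converge. This requires no assumption about which correlation pattern is true.

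The cost is about one sentence of wording and a standard R package. The model estimates six covariance parameters instead of two, from 140 planned participants. The downside is those few extra parameters and a small chance of non-convergence, which the fallback covers. The sample size need not change on this account.

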### Current intervention and research question

1.3

Powerly is a mental health mobile app, in which pregnant women can track their mood and level of stress and receive personalized psychological modules to increase their mental health and wellbeing. By integrating evidence-based content and cognitive behavioral techniques (CBT) with insights from pregnant and postpartum individuals and health professionals, Powerly offers a comprehensive psychological support. Full description of the development process and the app itself is presented in the Methods – “Intervention” section.

In this randomized clinical trial, we want to investigate Powerly's efficacy in terms of.

1) mental health symptoms, namely depressive symptoms, anxiety symptoms and level of stress,

2) emotion regulation and resilience outcomes, such as cognitive emotion regulation strategies, positive appraisal style, and self-efficacy,

3) mother & child outcomes, including mother-fetus/infant bond and satisfaction of birth, and Powerly's acceptability, indexed by the therapeutic alliance, app functionality rating as well as adherence.

In attempt to close the treatment gap, the app will be tested in conditions as close to real-life app use as possible. For instance, participants will not receive financial reimbursement for their time, and the control group will receive care as usual (CAU). If proven effective, this app will be made publicly available to women in need.

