#### Phase II – Development of leading therapeutic agents

2.1.2

Following the literature review, we integrated PCR and mental imagery as primary therapeutic components within Powerly.

Positive cognitive reappraisal was selected as a key stress resilience factor (Carlson et al., 2012; Kalisch et al., 2015). It has been successfully implemented in various therapeutic settings and proven effective in diverse contexts, as indicated by previous literature (Morello et al., 2023; Riepenhausen et al., 2022). Furthermore, individuals who can flexibly apply PCR techniques in response to the varying emotional demands of stressful situations tend to experience lower levels of perceived stress (Marciniak et al., 2024a). Given that pregnancy and early motherhood are often perceived as particularly stressful periods (Loomans et al., 2013), incorporating this component is essential. Within Powerly, pregnant individuals will be prompted to recall a recent stressful event and generate three possible reappraisals for this event. These reappraisals might include identifying unexpected benefits, learning something from the event, or considering advice they would give to someone facing a similar challenge. This particular module has been tested in two RCTs on a population of young adults in Switzerland who initially had a lower tendency to use PCR. It was found to be effective in increasing the use of PCR and in reducing anxiety symptoms, and highly feasible as indicated by over 80 % adherence (Marciniak et al., 2023).

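### The 'as-treated' analysis is a completer subset that only Powerly women can enter, so it has either no control group or a comparison that randomisation does not protect

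*Protocol article*

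**What the plan says.** Section 2.6.2 (Primary and secondary outcomes) sets the main analysis population: "We will employ intention-to-treat analyses, in which we will include all randomized participants, regardless of their app use". The same sentence adds a second analysis, "complemented by as-treated analyses, including participants who will complete at least one module per day".

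Section 2.5 (Procedure) describes the schedule for the Powerly arm: "They will be encouraged to use the app daily for 28 days, at least once per day". CAU women will "be informed that they will receive access to Powerly six weeks postpartum". After describing the final follow-up at six weeks postpartum, the section says: "After this, the CAU group will receive access to Powerly".

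The article does not say how CAU women enter the second analysis, or whether the daily criterion means each of the 28 days or an average over them. It describes no adjustment for selection into this set. It forecasts no adherence for this trial. The nearest figure is in section 2.1.2 (Phase II), where an earlier module tested in young Swiss adults is called "highly feasible as indicated by over 80 % adherence".

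**The concern.** App use is behaviour that occurs after randomisation. A rule that keeps participants because of it, when only one arm can show it, gives up the balance that randomisation created. Women who do an exercise every day for four weeks may well differ in motivation, mood and circumstances from those who do not. The Discussion already recognises motivation as a reason why women enrol, and it could equally influence who persists.

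The name adds to the problem. An as-treated analysis classifies all participants by the treatment they received. This rule drops participants by adherence, which makes it a per-protocol or completer analysis. A reader who trusts the label will misjudge what the estimate means.

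At stake is a supplementary result that invites the conclusion that the app works for those who use it, although the design cannot separate the effect of use from the kind of woman who uses it.

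**Working it through.** **1. Who can satisfy the rule.** Set sections 2.5 and 2.6.2 side by side. CAU women complete the final follow-up first and receive the app afterwards, so the number who can complete a module before their last outcome is 0 of 70. Two readings follow:

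- Literal: the rule applies to all participants. The control group is empty and there is no between-group comparison.
- Charitable: the rule applies to the Powerly arm only. A behaviour-selected part of one arm is compared with the whole of the other.

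Under neither reading does randomisation protect the comparison.

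**2. Size of the Powerly subset.** The plan has no figure of its own to reproduce. Inputs from the document: 70 women per arm (section 2.6.1) and 28 days (section 2.5). Assumed: every day is required, and mean daily completion m is 0.80 or 0.90.

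- Independent days: expected completers = 70 × m^28. At 0.80, 70 × 0.0019 = 0.1. At 0.90, 70 × 0.052 = 3.7. At 0.95, 70 × 0.238 = 16.6. At 0.98, 70 × 0.568 = 39.8.
- Days clustered within women (beta-binomial, intra-woman correlation ρ): P(all 28) = B(a + 28, b) / B(a, b), with a = m(1/ρ − 1) and b = (1 − m)(1/ρ − 1). Expected completers of 70:

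| Mean daily completion | ρ = 0.1 | ρ = 0.2 | ρ = 0.3 | ρ = 0.5 |
|---|---|---|---|---|
| 0.80 | 4.3 | 11.1 | 18.0 | 30.8 |
| 0.90 | 18.2 | 28.5 | 36.1 | 46.9 |

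The range is therefore about 0 to 31 at 80%, and about 4 to 47 at 90%. If the criterion is an average rather than every day, the subset could be larger still.

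**3. Precision under the charitable reading.** Two-sided t-test at 0.05 with the design effect d = 0.5 (section 2.6.1) and all 70 CAU women kept. Power is 0.31 with 10 completers, 0.50 with 20 and 0.67 with 35, against 0.84 for 70 versus 70. This is a simple two-sample comparison, not the planned mixed model.

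**4. Possible selection bias with no true effect.** Suppose adherence and outcome are jointly normal with correlation r, and the most adherent fraction f is kept. The mean outcome of the subset then shifts by r × φ(z)/f SD, where z is the upper-f normal quantile. For f = 0.20, φ(z)/f = 1.40:

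- r = 0.1: 0.14 SD
- r = 0.2: 0.28 SD
- r = 0.3: 0.42 SD

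The design effect is 0.5 SD. Both r and f are assumptions, and the shift is in outcome level.

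**The case against.** The strongest defence has four parts.

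- **Supplementary role.** Intention-to-treat on all randomised women comes first, and no conclusion stated in the article rests on the subset. This stands and limits the severity.
- **Natural reading and condensed format.** A rule about app use is most naturally applied to the arm that has the app, and a journal article may leave the handling of CAU women to a fuller document. This is fair as far as it goes. But the selection rule is stated here, and no further detail about CAU women would make it a randomised comparison unless the rule itself were replaced.
- **Numbers.** A reader might infer that almost nobody will qualify. The document does not support that. The very small figures need independent days, and they treat the earlier adherence figure of over 80% as a daily completion probability, which the article does not say it is. Clustering raises the expected number considerably. Section 2.1.4 does report poor adherence to digital behavioural activation in pregnant women, and section 1.3 says that "participants will not receive financial reimbursement for their time". These are reasons for caution, not a forecast. Only the empty CAU side, under the literal reading, is certain.
- **Bias.** A reader might also take 0.42 SD as the expected bias. It is the top of an assumed range. More distressed women might use the app more, which would reverse the sign. The planned model also includes baseline as a time point, so stable differences in mood may partly cancel, and the correlation that matters for a change-based contrast is the one with change. All of this stands. It makes the size and direction of the bias unknown, but does not remove it.

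**Conclusion.** The concern holds in a limited form. The analysis called as-treated is a completer subset chosen on post-randomisation behaviour that only one arm can show. It has no control group on the literal reading and a self-selected comparison on the charitable one. It cannot support a causal statement about the effect of Powerly when used. This conclusion follows from sections 2.5 and 2.6.2 alone and needs no assumption.

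The quantities are illustrative. The subset sizes depend on an assumed completion rate, on clustering and on reading the criterion as every day. The shift of 0.14 to 0.42 SD depends on an assumed correlation and on keeping the top 20%. The documents do not establish that the subset will be near-empty, that the bias has a known size or favours Powerly, or that the trial's main result is compromised. The point is worth correcting, but it does not threaten the intention-to-treat analysis.

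**What to change.** - Drop the label as-treated, and keep intention-to-treat as the main analysis.
- Replace the subset comparison with a complier-average causal effect, using randomised group as the instrument and all randomised women. Define compliance as any use of the app.
- If a higher threshold of use is preferred, state it in advance, state the assumption that women below it gain nothing, and vary that assumption in a sensitivity analysis. It matters. Suppose (assumed) that 60% reach the threshold with an effect of 0.5 and 40% are partial users with an effect of 0.25. The intention-to-treat effect is 0.6 × 0.5 + 0.4 × 0.25 = 0.40, and the complier estimate is 0.40/0.6 = 0.67, a third above the true 0.5.
- If a daily-completer or dose-response result is still wanted, say whether the criterion means each day or an average and how CAU women enter, and report it as exploratory and non-causal.

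The cost is a change of wording and a little R code. The interval will be wider than the subset comparison might show, and the estimate depends on the exclusion restriction, that is, on allocation affecting outcome only through the use counted as compliance.
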